### Statistical analysis

#### General principles

All analyses will be conducted using the full analysis set. Descriptive and exploratory analyses, including summary statistics, plots and data visualisation, will be performed using R (V.4.5.2 or higher). Multiple imputation for missing primary endpoint data and any associated confirmatory analyses will be performed using SAS (V.9.4 or higher) to ensure compliance with standard regulatory practices. Descriptive summary statistics will include the number of subjects (n), mean, SD, median, first and third quartiles (Q1 and Q3), minimum and maximum for continuous variables. Categorical variables will be summarised using counts and percentages, calculated either from the total number of subjects in the analysis population or from the number of subjects with available assessments, as appropriate. Two-sided 95% CIs will be presented where specified. All analyses will be performed in accordance with the study objectives and endpoints. Sensitivity analyses using multiple imputation will be performed in SAS for the primary endpoint. No sensitivity analyses are planned for secondary endpoints.

### Primary endpoint analysis

The primary objective of the study is to assess the durability of, and factors associated with, MVA-BN-specific antibodies at week 48 following a single vaccination dose. The primary endpoints of this study are

Mean geometric OPXV-specific antibody titres at week 48 postvaccination with MVA-BN in a population recruited in Africa.Mean rate of change in OPXV-specific antibody titres from week 6 to week 48 in a population recruited in Africa.

Antibody titres measured from baseline through Week 48 will be analysed using a linear mixed-effects model with log-transformed antibody titres as the dependent variable. To reflect the expected biological pattern of antibody titres following vaccination, time will be modelled as a continuous variable with a prespecified change point at week 6. This specification allows separate linear components for the expansion phase (baseline to week 6) and the waning phase (week 6 to week 48). Week 6 was selected a priori as the change point as this time point is expected to approximate peak vaccine-induced antibody responses following MVA-BN vaccination, thereby separating the early antibody expansion phase from the subsequent waning phase. The model will include fixed effects for time in each interval and a random intercept to account for within-participant correlation arising from repeated measurements.

The slope corresponding to the week 6 to week 48 interval will represent the primary durability parameter. An unstructured covariance matrix will be used to model the correlation among repeated measures within participants. If the unstructured covariance model fails to converge, alternative covariance structures, such as Toeplitz or heterogeneous first-order autoregressive (AR(1)), will be considered. Selection among competing covariance structures will be guided by the Akaike information criterion, balancing model fit and parsimony. Denominator df for fixed effects will be estimated using the Kenward-Roger approximation. The fitted mixed-effects model will be used to derive the model-estimated geometric mean titre at week 48 by back-transforming the least squares mean from the log scale, together with corresponding SEs and 95% CIs. The fixed-effect slope for the week 6 to week 48 interval will provide the estimated mean rate of change in log-transformed antibody titres during the waning phase, with corresponding 95% CIs. Results will be presented as model-estimated geometric mean titres with 95% CIs, estimated week 6 to week 48 slopes with 95% CIs and graphical displays of observed individual data with superimposed model-fitted trajectories over time.

The primary analysis of the endpoints will be conducted using observed data only (ie, without imputation of missing values) within the likelihood-based mixed-effects modelling framework. This approach accommodates incomplete repeated-measures data under the missing-at-random (MAR) assumption and provides the primary estimates of the geometric mean MVA-BN antibody titre at week 48 and the rate of change from week 6 to week 48. To inform the sensitivity analyses using multiple imputation, the extent and pattern of missing data will be summarised, including the proportion of participants with missing antibody titre measurements at each study visit and, where available, documented reasons for missingness. As part of the sensitivity analysis, multiple imputation will be performed under the assumption of MAR. Missing log-transformed antibody titres will be imputed using a model-based approach that includes all variables specified in the primary analysis model and incorporates the longitudinal structure of the repeated measurements. The number of imputations will depend on the overall proportion of missing data: 10 imputations will be generated if missingness is less than 10%, and 20 imputations will be generated if missingness is 10% or greater. Each imputed dataset will be analysed using the same piecewise mixed-effects model specified for the primary analysis. Estimates and associated standard errors will be combined across imputations using Rubin’s rules to obtain overall estimates and 95% CIs. Consistency between the primary observed-data analysis and the multiple imputation analysis will be assessed by comparing point estimates and corresponding 95% CIs for the week 48 geometric mean titre and the rate of change from week 6 to week 48. Differences will be considered material if they result in a meaningful change in the magnitude, direction or interpretation of the study conclusions.

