**Methods and analysis:**

Mpox-Vax AFRIVAC is a prospective, multicentre observational cohort study conducted in Uganda, Tanzania and the Democratic Republic of the Congo (DRC). Adults eligible for MVA-BN vaccination for mpox prevention or who received a first dose within 28 days prior to enrolment are followed for 48 weeks. Serial blood samples are collected to quantify binding antibody responses and assess their durability over time. The primary outcomes are mean geometric MVA-BN-specific antibody titres at week 48 and the rate of antibody decay from week 6 to week 48. Secondary outcomes include antibody kinetics at intermediate time points, factors associated with immune responses, breakthrough infection and vaccine safety. Analyses will use descriptive and longitudinal statistical methods to evaluate immune response trajectories and associated host factors, including HIV status, age and sex.

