### Participant recruitment and enrolment

Participants will be recruited at the ministry of health vaccination centres established in mpox hotspots identified through national surveillance. The study teams will work closely with the vaccination teams and community mobilisers to boost recruitment. Eligibility of the participants will be verified through vaccination cards, registration forms and national electronic vaccination records where available. Recruitment quotas have been predefined to ensure adequate representation of women and PWH, who are among the most affected in the ongoing clade 1b mpox outbreak. The study population has an a priori quota of:

25% participants who are people with HIV.50% female participants.

Written informed consent will be obtained from all participants by trained study staff prior to enrolment using participant information materials provided in appropriate local languages, with verbal explanation to ensure understanding. Consent will be documented in accordance with regulatory requirements.

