### Study timeline

Recruitment commenced in Uganda and the DRC in January 2025 following completion of regulatory approvals and site initiation activities. Although regulatory approvals were obtained in all participating countries, participant recruitment in Tanzania did not proceed due to limited vaccine availability. Enrolment is complete, with final participant follow-up anticipated to be completed in June 2026.

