### Endpoints

#### Primary endpoint

Mean geometric OPXV-specific antibody titres at week 48 post vaccination with MVA-BN in a population recruited in Africa.Mean rate of change in OPXV-specific antibody titres post week 6 to week 48 in a population recruited in Africa.

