### Sample size

We aim to have a 95% chance of obtaining a 90% CI (ie, an overall probability of achieving the desired precision and capturing the true mean with power of 0.95×0.9) whose half-width is at most 50 GMT. Assuming an expected SD of 485 GMT at week 48 (based on simulations using data from the Pittman *et al* phase III efficacy trial of MVA-BN vaccine),^8^ a sample size of approximately 300 participants would be required to achieve the desired level of accuracy around the mean GMT at week 48. To account for a potential 9% dropout rate, 330 participants will be recruited across three clinical sites.

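### The primary model and its multiple-imputation check leave out country, so dropout that differs between Uganda and the DRC would go unadjusted and unseen

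*Protocol article*

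**What the plan says.** Under Primary endpoint analysis, the article sets out a linear mixed model for log titre with a change point at week 6: "The model will include fixed effects for time in each interval and a random intercept". It goes on to fix the within-participant covariance, the fallback structures, the degrees of freedom and the back-transformation. No country or site term appears.

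The same section bases the primary result on observed data under missing at random. The stated sensitivity analysis is multiple imputation, also under missing at random, with a model that "includes all variables specified in the primary analysis model". Country is therefore not listed there either.

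The first primary endpoint is "Mean geometric OPXV-specific antibody titres at week 48 post vaccination with MVA-BN in a population recruited in Africa". The second is the mean rate of change from week 6 to week 48 in the same population.

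Study timeline reports that "participant recruitment in Tanzania did not proceed due to limited vaccine availability", which leaves Uganda and the DRC. Sample size still says that "330 participants will be recruited across three clinical sites". According to Study setting, Study medication and Laboratory procedures, the ministries of health vaccinate, a different institution in each country follows participants up, and samples are first processed locally. The HIV and sex quotas under Participant recruitment and enrolment are set for the study population as a whole.

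**The concern.** A likelihood-based mixed model handles dropout correctly only if missingness depends on what the model contains, here time and the participant's own observed titres. The random intercept absorbs a country difference in titre level. It does not absorb a country difference in the rate of waning. If antibodies wane faster in one country and that country also loses more participants before week 48, the late data come disproportionately from the slower-waning country. The fitted common slope and the week-48 GMT then drift towards that country, away from the average over everyone enrolled.

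The imputation check cannot reveal this, because it makes the same assumption with the same variables. Agreement between the two analyses would look reassuring without testing the point. Separately, one pooled line would hide any difference between Uganda and the DRC, although the Discussion itself suggests that background exposure and immune status may affect responses and intends the results to inform booster policy.

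**Working it through.** **1. The plan's own figure.** Inputs from Sample size: 95% assurance, 90% CI, half-width 50, SD 485, dropout 9%. The smallest n with P(t(0.95, n−1)·S/√n ≤ 50) ≥ 0.95 is 293, against the stated approximate 300. Then 300/(1 − 0.09) = 329.7, so 330. The sample size is reproduced. It does not depend on a country term and does not bear on this point.

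**2. When does omitting country matter?** The documents give no country split, retention or waning rate by country, so every input here is assumed. The simulations used 330 participants, a 50:50 split, natural-log titres, a 1.5-fold country difference in level and 40 runs per scenario. Only the paired differences between models should be read.

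| Assumed scenario | Week-48 log mean, without v with country | Slope per week, without v with country |
|---|---|---|
| Level differs, equal missingness | 4.755 v 4.755 | −0.01997 v −0.01997 |
| Level differs, unequal missingness | 4.759 v 4.762 | −0.01993 v −0.01984 |
| Level and slope differ, equal missingness | 4.953 v 4.953 | −0.01524 v −0.01523 |
| Level and slope differ, unequal missingness | 4.953 v 4.977 | −0.01545 v −0.01492 |

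Unequal missingness here means dropout of 5% v 25% and no week 0 sample in 20% v 80%. The slope difference is 0.01 per week. Only the last row separates visibly: exp(4.953 − 4.977) = 0.976, so the GMT is 2.4% lower without country. The slope gap is (0.01545 − 0.01492)/0.00093 ≈ 0.6 SE. Both conditions are needed.

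**3. How large?** Assume week 6 to 48 declines of 0.3 (country A) and 0.6 (country B) log10, 50:50, so the enrolled-mix decline is 0.450. As a rough guide, weight each country's decline by its week-48 retention. The SE of the decline is taken as 0.019 from simulation; it varies with the assumed SDs.

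| Missing at week 48, A v B | Overall | Retention-weighted decline | Shortfall | In SE | 10^shortfall |
|---|---|---|---|---|---|
| 9% v 9% | 9% | 0.450 | 0 | 0 | 1.00 |
| 5% v 13% | 9% | (0.95×0.3 + 0.87×0.6)/1.82 = 0.443 | 0.007 | 0.35 | 1.015 |
| 5% v 25% | 15% | (0.95×0.3 + 0.75×0.6)/1.70 = 0.432 | 0.018 | 0.93 | 1.04 |
| 3% v 35% | 19% | (0.97×0.3 + 0.65×0.6)/1.62 = 0.420 | 0.030 | 1.6 | 1.07 |

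Fitting the piecewise random-intercept model under these inputs gives similar answers:
- 5% v 13%: decline about 0.443, GMT about 1–2% high, 0.2–0.5 SE.
- 5% v 25%: GMT about 3% high, about 1 SE on the slope.
- 3% v 35%: decline 0.42, GMT about 4–6% high, roughly 1.1–1.7 SE.

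**4. Does the covariance or the proposed term repair it?** In the 3% v 35% case, an unstructured covariance without country leaves the bias nearly unchanged (decline 0.42, about 1.5 SE on the slope and 1.0 SE on the GMT). Adding country and country-by-time brings the decline to 0.448 and the GMT ratio to 0.997.

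**The case against.** The strongest reply is that this is a single-cohort, descriptive, precision-based study whose endpoints are defined for the pooled recruited population. Averaging over countries is what was asked for, and with equal missingness the two models agree. That stands: pooling is not an error.

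It is also fair that bias above one SE needs a twofold difference in waning together with 3% v 35% missingness. That is 19% overall, more than twice the planned 9%, and the documents support neither gap. With milder inputs (declines 0.4 v 0.5, missingness 3% v 15%) the GMT moves by under 1%. Even the sign depends on which country is less well retained: in step 2 the GMT falls, in step 3 it rises. The article also commits to summarising missingness and its reasons. All of this limits the size. It does not remove the gap, because the primary model is specified here and the stated imputation check shares its omission.

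A reader might go further and infer that the HIV comparison is confounded by country, since the quotas are study-wide. For scale, take 165 per country with 40% and 10% people with HIV (66 and 16.5 of 82.5), leaving 99 and 148.5 of 247.5 without HIV. A country GMT ratio r then gives a spurious HIV ratio of r^(66/82.5 − 99/247.5) = r^0.40, or 1.18 at r = 1.5; with equal HIV shares it is 1.00. But the quoted model has no HIV term. HIV enters through secondary endpoints, whose further analyses the article leaves to an SAP that is not shown and may already adjust for country. The documents give neither a country difference nor unequal HIV shares.

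Nor is the three-country wording in the Abstract and Sample size a concealed inconsistency. Study timeline and the Discussion explain openly that Tanzania did not enrol.

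**Conclusion.** The point holds in a limited form. As stated, neither the primary analysis nor its imputation check conditions on country, so missingness that depends on country is not handled if waning also differs by country, and neither analysis would show it. The likely size is modest: about 1–2% in the week-48 GMT and 0.2–0.5 SE at dropout near 9%, about 1 SE on the slope at 5% v 25%, and more only with very unequal dropout. These figures rest on an assumed equal country split, an assumed twofold difference in decline and assumed variances; no study-specific value can be computed from the documents. The documents do not show that the primary estimates are biased, or that the HIV, sex or age comparisons are confounded. The latter is a risk to check in the SAP.

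**What to change.** Before the analysis is run:

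- Add country and country-by-time for both phases to the primary model as fixed effects, or at least prespecify this as a sensitivity model. With two countries a fixed effect suits better than a random one.
- Standardise the overall week-48 GMT and week 6 to 48 slope to the enrolled country mix, so that the pooled target is kept.
- Include country in the imputation model.
- Report the week-48 GMT and the slope by country.
- Confirm that the SAP adjusts the HIV, sex and age analyses for country.
- As an editorial correction, update the Abstract and Sample size to two enrolling countries.

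The cost is three fixed effects (country and its interaction with each time phase), using information the study already holds, and a few lines of wording. Country-specific estimates will be less precise than the pooled ones and should be presented as such. Enrolment is complete and follow-up is expected to end in June 2026, so the change is most credible if it is fixed now.

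### The missing-data sensitivity analysis described for the primary endpoints keeps the primary model's missing-at-random assumption, so agreement between the two cannot show whether that assumption matters

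*Protocol article*

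**What the plan says.** All of this is in the Protocol article.

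- **Primary analysis (Primary endpoint analysis).** A likelihood mixed model is fitted to the observed log titres. On missing data the article says: "This approach accommodates incomplete repeated-measures data under the missing-at-random (MAR) assumption".
- **Content of that model (same section).** "The model will include fixed effects for time in each interval and a random intercept to account for within-participant correlation". HIV status, sex, age, country and enrolment route are not listed.
- **Sensitivity analysis (same section).** "As part of the sensitivity analysis, multiple imputation will be performed under the assumption of MAR". Missing log titres are imputed by a "model-based approach that includes all variables specified in the primary analysis model and incorporates the longitudinal structure of the repeated measurements".
- **After imputation (same section).** "Each imputed dataset will be analysed using the same piecewise mixed-effects model specified for the primary analysis". The estimates are pooled by Rubin's rules. Consistency is judged by setting the two sets of point estimates and 95% CIs side by side, for both the week-48 GMT and the week 6 to 48 slope.
- **Scope (General principles).** "Sensitivity analyses using multiple imputation will be performed in SAS for the primary endpoint. No sensitivity analyses are planned for secondary endpoints".

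The article also plans to summarise the proportion missing at each visit and the documented reasons. No analysis is tied to that summary.

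**The concern.** A sensitivity analysis for missing data is useful when it changes the assumption that the observed data cannot check. Here that assumption is that, given the titres already seen, participants without a week-48 sample would have had titres like those of participants who stayed. The planned imputation keeps this assumption and feeds the same analysis model.

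Both primary endpoints are exposed, because the week-48 GMT and the waning slope both depend on the last visit. The article's Introduction reports lower peak titres and faster decay in people with HIV, and the recruitment quota for them is 25%. If attendance at week 48 is related to HIV status beyond what earlier titres show, or to the unseen late titre itself, both analyses are off in the same direction. The planned comparison would then find them consistent.

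**Working it through.** **1. The plan's own figure.** Sample size states SD 485, a 90% CI with half-width at most 50, a 95% chance of achieving it, and 9% dropout. The smallest n for which the t-interval's half-width is at most 50 with probability at least 0.95 is 293; at n = 300 that probability is 0.978. Then 300/(1 − 0.09) = 329.7, or 330. The stated numbers reproduce, and 9% is taken as the planned missing share at week 48.

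**2. Size of the error that MAR methods leave.** Let p be the share missing at week 48. Let δ be the amount (log10) by which their unseen week-48 titres lie below what MAR predicts. Then:

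- error in the week-48 log10 mean = p × δ
- GMT too high by a factor of 10^(p × δ)
- error in the slope = p × δ / 42 per week, since 48 − 6 = 42

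The values of δ, and any p above 9%, are assumptions; the article gives neither.

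**3. Simulation of the planned comparison.** Each cohort had n = 330, with visits at weeks 0, 4, 6, 24 and 48, and a piecewise-linear mean with its change point at week 6. The observed-data analysis was maximum likelihood (ML) with unstructured covariance. It was compared with MAR multiple imputation (MI) from the same model, using 10 imputations below 10% missing and 20 otherwise, pooled by Rubin's rules. Assumptions: between-person SD 0.3 and within-person SD 0.2 log10, a slope of −0.012 log10 per week before any shift, half the participants without a week-0 sample, and 30 replicates per scenario.

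| p | δ | p × δ | GMT too high | ML bias (simulated) | MI bias (simulated) |
|---|---|---|---|---|---|
| 9% | 0 | 0 | 0% | +0.001 | +0.002 |
| 9% | 0.3 | 0.027 | 6% | +0.023 | +0.023 |
| 9% | 0.5 | 0.045 | 11% | +0.045 | +0.045 |
| 20% | 0.3 | 0.060 | 15% | +0.058 | +0.058 |
| 20% | 0.5 | 0.100 | 26% | +0.100 | +0.100 |

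The fourth column comes from the formula. The simulated biases match p × δ within Monte Carlo error: at SE 0.02 and 30 replicates, that error is about 0.02/√30 = 0.004.

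**4. Would the comparison show it?** Across all nine scenarios run (p = 9%, 20%, 30%; δ = 0, 0.3, 0.5), the mean absolute difference between ML and MI was 0.001 to 0.002 log10, with a maximum of 0.006. The SE was about 0.02. The two analyses agreed just as closely when both were wrong as when both were right.

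**5. Slope.** Both analyses estimated about −0.012 per week throughout. The true average slope is steeper by p × δ / 42:

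- p = 9%, δ = 0.3: 0.027/42 = 0.0006, giving −0.0126; waning is understated by 0.0006/0.0126, about 5%.
- p = 20%, δ = 0.5: 0.100/42 = 0.0024, giving −0.0144; waning is understated by 0.0024/0.0144, about 17%.

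**The case against.** Several points on the other side are sound and limit what can be said.

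- **The imputation model is a minimum specification.** A reader might infer that country, HIV status, sex and age are barred from it. The text says only that the model "includes all variables specified in the primary analysis model and incorporates the longitudinal structure of the repeated measurements". Auxiliary variables are unnamed, not excluded.
- **Agreement is not guaranteed.** A reader might infer that the two analyses must coincide. A further check imputed with unrestricted visit means and then fitted the piecewise model (n = 330, 12 replicates per scenario, assumed SDs). Under linear waning the two agreed within 0.002 log10. Under curved waning with about 18 to 19% missing they differed by 0.009 to 0.028 log10, about 2 to 7%. Such a gap reflects the form of the model and still does not test MAR.
- **The article does not claim robustness.** It speaks of consistency and of material differences. Reading agreement as proof of robustness is an inference, though an easy one to draw from the comparison.
- **MAR likelihood already handles part of the threat.** Dropout related to earlier observed titres is covered. What remains is dependence on the unseen titre, or on HIV status given earlier titres.
- **The size may be small.** With a milder assumed mechanism (odds ratio e per SD of week-48 titre), the bias was 0.012 to 0.014 log10, about 3%, at 9 to 10% missing.
- **Week 0.** A reader might infer that week-0 titres never scheduled for participants enrolled after their dose would be imputed. The wording is ambiguous, but missing can fairly mean scheduled and not obtained, and no effect on week 48 was shown.
- **The analysis plan is not shown.** It may contain more, and General principles speaks of multiple imputation without fixing MAR. But the article itself fixes the assumption, minimum variables, number of imputations, pooling and comparison. This is therefore a stated choice, not a detail left out.

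**Conclusion.** The point holds in limited form. The one missing-data sensitivity analysis that the article describes for the primary endpoints does not vary the assumption in doubt, so its agreement with the primary result is uninformative about lower unseen titres in participants missing at week 48.

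At the planned 9% dropout the effect is modest. A shift of 0.3 log10 makes the GMT about 6% too high, against a 95% CI of roughly ±9% under the simulation's SDs (1.96 × 0.02 = 0.039; 10^0.039 = 1.09). It grows with the missing share, to about 15% at 20% missing with the same shift. In both analyses waning looks slower than it is.

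These sizes rest on assumed shifts, SDs and missing shares. The documents do not support saying that the primary result will be biased, only that this check could not reveal it if it were. The change is worth making but does not undermine the primary analysis.

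**What to change.** 1. Keep the MAR imputation, labelled as supportive.
2. Name auxiliary variables for the imputation model from data already collected: country, HIV status and history of advanced HIV disease, sex, age, and enrolment before or after the dose.
3. Add a delta-adjusted (pattern-mixture) imputation. After imputing under MAR, shift the imputed log10 titres at visits after week 6 over a prespecified range, for example 0 to −0.5 log10, stated as an assumption.
4. At each shift, report the week-48 GMT and the week 6 to 48 slope with 95% CIs. A tipping point should not be reported: this is a single-group precision study with no decision threshold for either endpoint.

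The cost is a short addition to the SAS code, revised wording and one more table; no new data are needed. The real burden is that the width and direction of the delta range must be justified, preferably before the week-48 titres are analysed.
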